### Data analysis

A full statistical analysis plan will be developed before any data are analyzed. The analysis and presentation of the trial will be in accordance with CONSORT guidelines for cluster randomized trials [46, 47]. The primary approach for comparative analyses will be to analyze participants as randomized without imputation of missing data, and with due emphasis placed on confidence intervals for the between-arm comparisons. We will use descriptive statistics to assess balance between the trial arms at baseline for both clinic and individual participant characteristics. In order to take appropriate account of the hierarchical nature of the data, we will use multivariable mixed effects regression models to estimate recovery from depression at 6 months for intervention group versus control, adjusting for baseline depression and LGA as a stratification variable. In a secondary analysis, we will further adjust for any variables that were imbalanced between trial arms at baseline. These analyses will be repeated for secondary outcomes. We will conduct sensitivity analyses to assess the potential effect of missing data, and will investigate the effect of adherence with the intervention. We will investigate whether between-group differences vary over time using data from all follow-up visits in repeated measures analyses.

We will investigate whether there is any differential effect of the intervention according to baseline symptom severity (EPDS score <16, ≥16) by including appropriate interaction terms in the primary regression model. Since the trial is powered to detect overall differences between groups rather than interactions of this kind, the results will be interpreted with due caution.

Data analysis will be conducted once all follow-up is complete. There are no planned interim analyses.

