**Methods/Study design:**

A pragmatic two-arm parallel cluster randomized controlled trial was designed. The units of allocation are the primary maternal care clinics. Thirty eligible and consenting clinics were randomized but, due to problems with logistics, 29 eventually participated. Consenting pregnant women with a gestational age between 16 and 28 weeks who screened positive on the Edinburgh Postnatal Depression Scale (EPDS score ≥12), absent psychosis or bipolar disorder, and not actively suicidal were recruited into the trial (N = 686). Midwives in the intervention arm were trained to deliver psychoeducation, problem solving treatment, and parenting skills. Eight weekly sessions were delivered following entry into the study. Further sessions during pregnancy and 6 weeks following childbirth were determined by level of depressive symptoms. Clinical support and supervision, delivered mainly by mobile phone, were provided by general physicians and psychiatrists. Automated text and voice messages, also delivered by mobile phones, were used to facilitate patient compliance with clinic appointments and ‘homework’ tasks. Patients in the control arm received care as usual enhanced by further training of the providers in that arm in the recognition and standard treatment of depression. Assessments are undertaken at baseline, 2 months following recruitment into the study and 3, 6, 9 and 12 months after childbirth. The primary outcome is recovery from depression (EPDS < 6) at 6 months. Secondary outcomes include measures of disability, parenting skills, maternal attitudes, health care utilization as well as infant physical and cognitive development comprehensively assessed using the Bayley’s Scales.

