### Outcome measures

The outcome assessments, still on-going at the time of this report, are conducted mostly in the patients’ homes (except when patient prefers to have the assessment elsewhere) by the trained research staff. Outcome assessors have no involvement in delivering the intervention and are rotated between MCCs to collect outcome data. All consenting patients receive baseline assessment within 72 h of being screened and consenting to enter the trial. Follow-up assessments are conducted at 2 months following recruitment into the study and 3, 6, 9 and 12 months after childbirth. All scales are administered in their Yoruba versions, derived through standard iterative procedures which we have employed in previous studies.

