### Secondary outcomes

Score on the EPDS: in order to address the possibility that even though individuals may have recovered from a major depressive disorder, significant depressive symptoms may still persist. The EPDS is a 10-item screening instrument for depression. It has been validated and used in earlier studies of perinatal depression in Nigeria [11].Disability in the mother is assessed using the WHO Disability Assessment Scale [37], previously used by us [38];Parenting skills (measured as maternal attitude and adjustment to parenting) using the Maternal Adjustment and Maternal Attitudes Questionnaire (MAMAs), a widely used questionnaire with good acceptability to women and good reliability [39] as well as the Infant Toddler version of the Home Inventory for Measurement of the Environment (HOME-IT) [40]An adapted version of the experience of stigma by mothers with the 12-item Discrimination and Stigma Scale, a cross-culturally valid tool that has been previously used among Nigerian subjects [41]The Client Service Receipt Inventory-PND version [42], an adaptation of the Service Utilization Questionnaire (SUQ) which we have used in previous studies to assess health service utilization [43]Infant development: the child’s current level of cognitive, language, personal-social, and fine and gross motor development with an infant well-being questionnaire. This questionnaire was developed by us and it incorporates questions on child nutrition, achievement of developmental milestones, illnesses, immunization and measurements of the length/height and weight and administered at 3, 6, 9 and 12 months. At 12 months, a comprehensive assessment of motor and cognitive development is conducted using the Bayley Scales of Infant Development [44] which has been used previously among Nigerian subjects [45].

The times and components of all scheduled outcome assessments are shown in Fig. 2. Outcome data is collected from every participant not known to have died at the time of follow-up and who has not withdrawn consent, regardless of compliance with allocated treatment.

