### Sample size

Experience from our previous studies in primary health care (PHC) as well as from the control arm of a Pakistani trial among women with perinatal depression suggests a recovery rate of about 45 % for major depression with no active treatment and about 75 % with treatment [29]. In a Chilean study of postnatal women with depression, using a 3-point reduction in baseline score of the depression assessment tool, remission rate was 57 % with no active treatment and 73 % with active treatment [28]. For our sample size estimation, we sought to detect an absolute difference of 15 percentage points (40 % recovery in control and 55 % in intervention groups respectively) at 6 months, a difference that we think is both plausible for this type of intervention and would promote changes in practice. In our pilot study among antenatal women, we observed an intra-cluster correlation coefficient (ICC) of 0.026 for EPDS scores. In our pilot study among general adults with depression, we were able to collect primary outcome at 6 months from 87.8 % of the participants. We expect a higher follow-up rate among perinatal women who generally are less likely to move. However, we will use a conservative 6-month follow-up rate of 85 % for our estimate. We also assume a 7 % infant death rate within the period. The uninflated sample size requires 186 per arm for analysis to detect a difference of 55 % vs 40 % (equivalent odds ratio = 1.8) with 80 % power at the two-sided 5 % alpha level. We originally aimed to recruit 50 individuals per MCC. With 43 individuals per cluster available for the primary analysis and an ICC of 0.026, the design effect is 2.09 giving a total number required for analysis of 778. We therefore aimed to recruit a total of 916 individuals from a total of 18 MCCs. As participant recruitment was slower than anticipated, in January 2014 we recruited and randomised a further 11 MCCs, giving a total of 29 in the study. Participant recruitment took place between July 2013 and October 2014. Outcome assessments are still ongoing and will continue till one year post-delivery assessment is concluded for the last recruited participant.

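### Read literally, secondary outcomes carry over the primary model's covariates, so an outcome's own baseline value enters only if imbalanced; where a continuous maternal scale was recorded at baseline, this gives up some precision.

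*Protocol article*

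**What the plan says.** The Data analysis section of the protocol article specifies a mixed effects regression for recovery at 6 months, "adjusting for baseline depression and LGA as a stratification variable". It adds a secondary analysis in which "we will further adjust for any variables that were imbalanced between trial arms at baseline". The next sentence extends both to the other endpoints: "These analyses will be repeated for secondary outcomes". No outcome-specific baseline covariate is named, and none is ruled out. The section opens by deferring detail: "A full statistical analysis plan will be developed before any data are analyzed".

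On what is measured at baseline, the Outcome measures section says "All consenting patients receive baseline assessment within 72 h of being screened and consenting to enter the trial" but does not list the instruments. The Secondary outcomes section refers to a figure for that: "The times and components of all scheduled outcome assessments are shown in Fig. 2". The figure is not reproduced in the text available. The maternal secondary outcomes named are the EPDS score, disability, parenting skills and attitudes (two instruments), stigma and service use.

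**The concern.** Baseline depression is a natural covariate for recovery from depression, because it is the starting value of the scale that defines the outcome. Carried unchanged to a disability or stigma score, it becomes a proxy. The starting value of the same scale is usually the stronger predictor. Entry also requires an EPDS of 12 or more, which restricts the range of baseline EPDS and tends to weaken it as a predictor of other scales.

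The imbalance rule does not fully close the gap. It admits a baseline value because the arms happen to differ on it, not because it predicts the outcome, and it does so only in a further analysis. The main estimate for each such scale would still lack the covariate.

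What is at stake is the width of the confidence intervals for some maternal secondary outcomes. Recruitment reached 686 women in 29 clinics, against a target of 916, so precision that needs no new data is worth having.

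**Working it through.** **The plan's own figures.** The article gives no precision or power figure for any secondary outcome. Its primary sample size reproduces and is not affected by this point:
- 40% against 55%, "with 80 % power at the two-sided 5 % alpha level": 173 per arm without continuity correction and 186 with it, which matches the stated 186.
- Design effect 1 + (43 − 1) × 0.026 = 2.092, and 2 × 186 × 2.092 = 778.
- 778 / 0.85 = 915.3, rounded up to 916.

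**Which outcomes can be affected.**
- EPDS score: baseline depression is its own baseline, so nothing is lost.
- Infant outcomes, and the home-environment inventory, which presupposes an infant: enrolment is at 16 to 28 weeks' gestation, so there is no baseline value.
- Disability, stigma, maternal attitudes, service use: affected only if recorded at baseline, which the visible text does not show. The formula below is for a continuous outcome in a linear model and is not shown to suit service-use data.

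**Gain from adding the own baseline to a model that already has baseline EPDS.** Let a be the correlation of the outcome with its own baseline, b its correlation with baseline EPDS, and c the correlation between the two baselines. None is in the article; all are assumed.
- Residual variance with EPDS only: V0 = 1 − b².
- Residual variance with both: V1 = 1 − (a² + b² − 2abc) / (1 − c²).
- Relative standard error: √(V1/V0). Equivalent increase in participants: V0/V1 − 1.

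One case in full, a = 0.6, b = 0.3, c = 0.4: V0 = 1 − 0.09 = 0.910. V1 = 1 − (0.36 + 0.09 − 0.144) / 0.84 = 1 − 0.364 = 0.636. V1/V0 = 0.699, so the standard error is 16% smaller, worth 1/0.699 − 1 = 43% more participants.

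| a | b | c | V0 | V1 | V1/V0 | SE smaller by | Worth more participants |
|---|---|---|---|---|---|---|---|
| 0.3 | 0.4 | 0.5 | 0.840 | 0.827 | 0.984 | 0.8% | 1.6% |
| 0.3 | 0.3 | 0.5 | 0.910 | 0.880 | 0.967 | 1.7% | 3% |
| 0.3 | 0.3 | 0.4 | 0.910 | 0.871 | 0.958 | 2% | 4% |
| 0.5 | 0.3 | 0.4 | 0.910 | 0.738 | 0.811 | 10% | 23% |
| 0.6 | 0.4 | 0.5 | 0.840 | 0.627 | 0.746 | 14% | 34% |
| 0.6 | 0.3 | 0.4 | 0.910 | 0.636 | 0.699 | 16% | 43% |

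The range is therefore roughly 3% to 43%. The first row, the least favourable corner of the assumed ranges, falls to about 2%. The equivalence takes the design effect as unchanged, so it means more clinics of the same size.

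**In outcome units.** Assume 85% follow-up of 686 women (583 analysed), 29 clinics averaging 20.1 each, and the pilot EPDS intra-cluster correlation of 0.026 for the other scales. The design effect is 1 + 19.1 × 0.026 = 1.50 and the effective total is about 390, or 195 per arm. The difference detectable with 80% power is 2.80 × √(2V/195) standard deviations. With b = 0.3 and EPDS adjustment only, this is 0.27. Adding the own baseline (c = 0.4) gives 0.26 for a = 0.3, 0.24 for a = 0.5 and 0.23 for a = 0.6.

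**The case against.** The strongest reply is that this is a one-sentence summary in a journal article that promises a full analysis plan, and that covariates for each secondary outcome are normally settled there. Adjusting for baseline depression and local government area is a valid prespecified model. Baseline depression is also the primary outcome's own baseline, so repeating the analyses could mean using the analogous baseline for each outcome. Much of this stands: the article does not exclude own baselines, and the plan may already name them. What remains is that the article states a covariate set and a rule for carrying it over, and the literal reading of that rule is the less efficient one.

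The documents do not support several stronger readings that a reader might infer:
- That precision is certainly lost on disability, stigma and service use. The visible text does not show that these were recorded at baseline. If they were not, the wording costs nothing.
- That chance baseline differences go uncorrected. The imbalance-adjusted analysis is also repeated for secondary outcomes and would pick up a differing baseline score, though not in the main estimate.
- That the gain is 10% to 56%. That is 1/(1 − a²) − 1 for a of 0.3 to 0.6, which compares with no baseline covariate at all. The plan already adjusts for baseline EPDS.
- That the model is biased. Leaving out a prognostic covariate does not by itself bias a randomised comparison. Women were recruited after clinics were allocated, so differential recruitment is conceivable, but the article shows no evidence of it.

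It could also be said that the own baseline may predict no better than the EPDS. If it replaced the EPDS, the standard error could indeed rise, for example by 4% with a = 0.3 and b = 0.4. The change proposed here adds it instead. For a continuous outcome this cannot raise residual variance, apart from about one degree of freedom.

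**Conclusion.** The point holds as a minor, conditional efficiency improvement. By its literal wording, the Data analysis section gives scales other than the EPDS a main adjusted estimate without their own baseline value. For a continuous maternal scale recorded at baseline, the forgone gain ranges from almost nothing to a standard error about 16% smaller.

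That size rests on three assumptions the article cannot confirm: that the scale was recorded at baseline, that the correlations lie in the ranges used, and that the design effect is unchanged by the extra covariate. The primary analysis, the sample size, the EPDS score and the infant outcomes are not touched. If the analysis plan already specifies own-baseline adjustment, nothing remains to be done.

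**What to change.** State in the Data analysis section, or confirm in the statistical analysis plan: *Each secondary outcome will be analysed with the same model, adjusting for LGA, baseline EPDS and, where recorded at the baseline assessment, the baseline value of that outcome, irrespective of any observed imbalance between arms.*

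The plan should also list which scales have a baseline value, taken from the assessment schedule. The cost is one clause and one extra covariate per affected model. No new data are needed. The article says the plan will be written before any data are analysed, so the clause can still be prespecified.

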## Discussion

EXPONATE is designed to provide empirical data that will improve our understanding of the management of perinatal depression in resource-constrained settings. Its findings should inform the development of programs to scale-up feasible and effective intervention through primary maternal care service.

## Abbreviations

LMIC: Low and middle income countries
EPDS: Edinburgh postnatal depression scale
CHW: Community health worker
CMW: Community midwives
LGA: Local government area
MCC: Maternal and child care clinic
MHGAP-IG: WHO mental health gap action programme intervention guide
PST: Problem solving treatment
PHC: Primary health care
